# The effect of phasic versus combined neuromuscular electrical stimulation using the StimaWELL 120MTRS system on multifidus muscle morphology and function in patients with chronic low back pain: a randomized controlled trial protocol

**DOI:** 10.1186/s12891-022-05578-1

**Published:** 2022-07-01

**Keywords:** Low back pain, Electrical stimulation therapy, Multifidus muscle, MRI, Ultrasound

## Abstract

**Background:**

Neuromuscular electrical stimulation (NMES) is used to improve muscle strength clinically when rehabilitating various musculoskeletal disorders. However, the effects of NMES on muscle morphology and function in individuals with non-specific chronic low back pain (CLBP) have scarcely been investigated. Although research links deficits in the paraspinal musculature with subjective reports of pain and disability, it is unknown if treatment with NMES can help reverse these deficits. Therefore, the primary aim of this study is to compare the effects of two muscle therapy protocols with a medium-frequency electrotherapy device (the StimaWELL 120MTRS system) on multifidus muscle morphology and function in CLBP patients. The secondary aims are to determine the effects of these protocols subjective reports of pain intensity, pain interference, disability, and catastrophizing.

**Methods:**

A total of 30 participants with non-specific CLBP, aged 18–60, will be recruited from local orthopedic clinics and databases. Participants will be randomized (1:1) to either the phasic or combined (phasic + tonic) muscle therapy protocols on the StimaWELL 120MTRS system. Participants will undergo 20 supervised electrotherapy treatments over a 10-week period. The primary outcomes will be multifidus morphology (e.g. cross-sectional area (CSA), fat infiltration) and function (e.g., contraction measured via %thickness change from a rested to contracted state, and stiffness at rest and during contraction). Secondary outcomes will include pain intensity, interference, disability, and catastrophizing. Both primary and secondary outcomes will be obtained at baseline and at 11-weeks; secondary outcomes measured via questionnaires will also be obtained at 6-weeks, while LBP intensity will be measured before and after each treatment. Paired t-tests will be used to assess within-group changes for all primary outcome measures. A two-way repeated-measures analysis of variance will be used to assess changes in secondary outcomes over time.

**Discussion:**

The results of this trial will help clarify the role of medium-frequency NMES on lumbar multifidus morphology and function.

**Trial Registration:**

NCT04891692, registered retrospectively on May 18, 2021.

## Background

Chronic low-back pain (CLBP) is the leading cause of years lived with disability globally[1]. It poses a significant financial burden to health-care systems: in Canada alone, healthcare costs for low back pain range from $6 to $12 billion annually[2, 3]. The vast majority of CLBP cases are of unknown etiology, meaning that a link between pain and a specific pain-generating structure cannot be established[4]. Nevertheless, research suggests that CLBP patients have deficits in the lumbar multifidus[5], a local back muscle which helps with spinal stability and load transfer[6].

There is evidence of morphological and functional changes in the multifidus in individuals with CLBP, including increased fat infiltration[7], increased stiffness at rest[8, 9], and decreased cross-sectional area (CSA)[10], which is negatively correlated with the muscle’s ability to produce force[7]. Murillo et al. found increased stiffness in the fibers of the superficial multifidus (SM), as well as decreased stiffness with contraction, in individuals with CLBP compared with healthy controls.[9] In addition, people suffering from LBP have a harder time voluntarily activating the multifidus.[11] There are theoretical rationales behind these changes. A decrease in CSA occurs with disuse and atrophy, while fatty and fibrotic infiltration reduces muscle quality, impacting the contractile output of the muscle.[12] Abnormalities in multifidus stiffness might be related to 1) elevated sympathetic nervous system activity leading to increased muscle tone in the superficial multifidus, and 2) a shift in multifidus fiber type from type II to the stiffer type I fibers[9]. Given the link between CLBP and multifidus muscle deficits, interventions that can reverse these deficits should have promising clinical outcomes.

There is mixed evidence as to whether exercise therapy, a common conservative CLBP intervention, can induce morphological and functional changes in the lumbar multifidus. Recent studies suggest that motor control exercises[13],stabilization exercises[14, 15], and high-load exercises[13](i.e., deadlift) may be effective at improving lumbar multifidus stiffness. On the other hand, a study using a machine-based, resistance exercise program saw no effects on multifidus CSA or fat infiltration[16]. Regardless, exercise therapy is not always a feasible modality. Individuals with fear-avoidance behaviors may be unwilling to engage or have reduced compliance with regards to exercise, while others with reduced mobility and function may find exercise interventions unsustainable, if not impossible. If other modalities are shown to be effective at improving lumbar multifidus morphology and function, it will alleviate the burden on exercise therapy to fulfill this role, and a wider scope of CLBP patients will benefit from conservative treatment.

Electrical stimulation therapy is a treatment modality commonly used to treat pain and muscle dysfunction. Specifically, clinicians use neuromuscular electrical stimulation (NMES) to restore strength and muscle function following atrophy or loss of neuromuscular control. NMES preferentially stimulates alpha motor neurons, causing involuntary muscular contraction. Over time, the treatment can help individuals relearn how to voluntarily contract the target muscle and improve patient outcomes[17]. NMES has been used most extensively on the quadriceps muscle, with evidence that it improves quadricep cross-sectional area following atrophy, with and without voluntary contraction[18]. However, research into its effect on lumbar multifidus morphology, as assessed with MRI or ultrasound, is very limited. Coghlan et al. (2011) reported that a 6-week NMES intervention improved resting, but not contracting, multifidus thickness in CLBP patients.[19] A recent study investigating the effect of a 4-week Russian current intervention in young women with CLBP found a non-statistically significant increase in lumbar multifidus thickness, with medium effect sizes.[20] The results from NMES interventions on CLBP patient outcomes more broadly are also mixed. Hicks et al. (2016) trial found that combined trunk muscle training with NMES was more effective than a passive control intervention (heat + ultrasound + massage) at improving performance-based and self-rated function in older adults with CLBP.[21] Another study investigated the effect of a 4-week NMES protocol on CLBP patients saw no improvement in disability compared with matched controls[22], while Alrwaily et al. (2019) reported no additional benefit of NMES on self-reported pain and disability, fear-avoidance beliefs, and paraspinal muscle strength following a stabilization exercise program and combined stabilization + NMES program in patients with CLBP patients.[23]

In all but one of the studies cited above, researchers used traditional NMES protocols, in which the current is delivered at ranges of 10–100 Hz[24].This frequency range is sometimes described as being uncomfortable for patients, because skin impedance to current is thought to be inversely proportional to stimulation frequency[17, 18]. Medium-frequency electrical stimulation therapy, delivered at ranges of 1-10 kHz, is considered by advocates to penetrate the skin more easily than low-frequency stimulation. Proponents claim this makes it both more effective at muscle stimulation, and more comfortable for patients. Tolerance to treatment is critical because patients who tolerate higher current intensities experience greater real-time multifidus thickening[25, 26], which may lead to hypertrophic and strength gains over time. To date, the effects of medium-frequency electrical stimulation therapy on multifidus muscle morphology and function in CLBP have not been investigated. Therefore, the primary aim of this study is to investigate the effects of a 10-week muscle therapy intervention using the StimaWELL 120MTRS system (a medium-frequency electrotherapy device) on multifidus muscle morphology and function. Secondary aims are to investigate its effect on pain intensity, pain interference, pain catastrophizing, and disability.

## Methods

### Study design

The proposed study is a two-arm randomized controlled trial with test–retest design. 30 participants will be recruited and randomized into one of two muscle therapy protocols for the lumbar spine: the ‘phasic’ group (*n* = 15) or the ‘combined’ group (*n* = 15) (Fig. 1).

**Fig. 1 Fig1:**
[figure not shown]
Consort Flow Diagram

### Study setting

This trial will be conducted at the PERFORM Centre (Concordia University, Montreal, QC, Canada). The proposed trial was developed in accordance with the SPIRIT guidelines and approved by the Central Ethics Research Committee of the Quebec Minister of Health and Social Services (#CCER-20–21-07). All participants will be required to sign an informed consent form prior to beginning the study.

### Participant recruitment

Participants will be recruited by students and clinicians affiliated with the Quebec Low Back Pain Consortium, through the PERFORM Centre’s website and mailing list, over social media (Facebook, Instagram), and through word-of-mouth. Individuals affiliated with the Quebec Low Back Pain Consortium who agree to be contacted for studies will receive either a telephone call or email explaining the study aims and procedure. All prospective participants will undergo a preliminary phone screening to verify eligibility. Those who pass the phone screen will be invited to the PERFORM Centre for a neurological screen, and a trial visit with the StimaWELL 120MTRS system.

### Participants

#### Inclusion Criteria

Participants must meet all the following criteria for inclusion:Chronic non-specific LBP (> 3 months), defined as pain in the region between the lower ribs and gluteal folds, with or without leg pain.Aged between 18 to 60 years old.English or French speakersHave at least score of ‘moderate’ on the Modified Oswestry Disability Index (ODI) (to ensure a minimal important change [MIC] is detectable)[27].Able to undergo MRI exam

#### Exclusion Criteria

Participants will be excluded if they meet any of the following criteria:Currently undergoing or having received physical therapy treatment in the previous monthConsistent motor control training for the low back and / or consistent weightlifting, powerlifting, bodybuilding, or strongman training in the previous 6 weeks (resistance training is a potential confounding variable; however, muscle strength and size decreases 2–6 weeks following the cessation of resistance training in both trained and un-trained individuals[28, 29].)History of lumbar surgeryPresence of positive lumbosacral dermatomes or myotomesPresence of disease which could affect the stiffness of muscle tissue (collagen tissue disease, hemiplegia, multiple sclerosis, blood clots)Presence of systemic disease (cancer, metabolic syndrome)Presence of spinal abnormality (spinal stenosis, fracture, infection, tumor**,** or lumbar scoliosis greater than 10 degrees)BMI > 30 (subcutaneous fat attenuates ultrasound signal and can invalidate measurements in obese individuals)[30].Presence of cardiac arrhythmiaPregnant and breastfeeding womenIndividuals with epilepsyIndividuals at risk for serious bleedingIndividuals with pacemakers or metal implantsIndividuals with aneurysms or heart valve clipsIndividuals who have taken prescribed muscle relaxants more than once a week in the previous month

### Randomization

Participants will be randomized to treatment groups (1:1) using consecutively numbered sealed opaque envelopes (e.g., computer-generated randomization sequences) created by an individual not involved in the study.

### Personnel

A PhD student (who is a certified athletic therapist), not blinded to group allocation, will conduct most in-person activities, including neurological testing, ultrasound evaluations, and intervention administration. In Canada, certified athletic therapists are health-care practitioners who specialize in the prevention, assessment, and treatment of musculoskeletal injuries. A PERFORM Centre technician will administer the MRI exam. Participant recruitment and preliminary screening will be conducted jointly between the PhD student and a research assistant working for this study’s primary investigator.

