### Primary outcome measures

#### MRI assessment of multifidus morphology

All participants will undergo a lumbosacral MRI evaluation using the PERFORM Centre’s 3-T GE machine to assess multifidus muscle CSA and fat infiltration. MR imaging will be collected using a standard phased-array body coil with 4-mm slice thickness, 180-mm2 field of view and 512 × 512 matrix. Quantitative multifidus muscle measurements will be obtained from axial T2-weighted images, bilaterally at the L4-L5 and L5-S1 spinal levels, which are the most relevant levels for spinal pathologies. The multifidus muscle CSA will be measured manually at both levels on multiple slices to calculate the summative 3D volume; cross-sectional area measurements have been widely used to assess muscle size and this technique is very reliable (ICCs:0.97–0.99)[33]. Multifidus muscle composition (e.g., fatty infiltration) will be assessed using IDEAL (Lava-flex, 2 echo sequence) fat and water images by calculating percent-fat signal fraction at each spinal level according to the following equation: %FSF = (Signal_fat_/[Signal_water_ + Signal_Fat_] × 100)[34].

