#### Ultrasound assessment of multifidus muscle function

The PERFORM Centre’s Aixplorer ultrasound unit (Supersonic Imagine, Aix-en-Provence, France) will be used to assess multifidus muscle contraction and stiffness. First, participants will be placed in a prone position, on a therapy table, with a pillow placed under their abdomen to minimize lumbar lordosis (e.g., maximum of 10° measured with an inclinometer) and instructed to relax the paraspinal musculature. The spinous process of L5 will be palpated and marked on the skin with a pen prior to imaging. Acoustic coupling gel will be applied to the skin and the ultrasound transducer placed longitudinally along the midline of the lumbar spine to confirm the location of the L5 level. The multifidus muscle will be imaged bilaterally, in the parasagittal section, allowing for the visualization of the L5/S1 zygapophyseal joints. Multifidus muscle contraction, expressed as the % thickness change from a rested to contracted position, will be assessed via contralateral arm lifts while holding a small handheld weight (e.g., 1.5 to 3 pounds) based on the participant’s body weight. Participants will be instructed to raise the loaded arm 5 cm off the examination table with the shoulder in 120° of abduction and elbow 90° of flexion, following a deep inhalation and exhalation. Images will be taken after the loaded arm has been held for 5 s. The handed weight is designed to load the multifidus muscle to approximately 30% of maximal voluntary isometric contraction. Measurements will be obtained at L4-L5 and L5-S1 and repeated 3 times, both at rest and during contraction on each side. The average of 3 thickness ratios ([thickness contracted – thickness rest / thickness rest] × 100) will be calculated in used in the analysis. This technique is valid and reliable[35, 36].

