The same position and procedure will be used to assess multifidus muscle stiffness with shear-wave elastography. This technique is based on a compressive wave that propagates within the tissue, allowing for the calculation of tissue shear wave modulus while rendering a quantitative color-coded map of tissue elasticity. Participants will be lying prone on the therapy table for 5 min before the lumbar multifidus is imaged at rest and during sub-maximal contractions while performing the same task as described above. Three repetitions will be performed on each side (both at L4-L5 and L5-S1) and the average shear wave modulus will be used for analysis. Finally, multifidus muscle stiffness will also be examined in a standing position when the muscle is naturally contracting in a stabilizing role. Participants will be asked to stand barefoot on the floor with their arms relaxed on each side. To achieve a habitual standing posture, they will be instructed to march on a spot for a few seconds and remain on the position where their feet landed. Resting shear wave modulus measurements will be acquired as described above and obtained in the standing fundamental position (e.g., arms resting naturally on each side of the body). Again, three measurements will be obtained on each side (both at L4-L5 and L5-S1) and the average shear wave modulus will be used in the analysis. This technique is valid and reliable[37–39].

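### The unblinded treating therapist also acquires the ultrasound primary outcomes; masked reading of coded images would limit the observer bias this allows, most of all in the pre-post tests

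*Protocol article*

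**What the plan says.** - **Who measures.** The Personnel section says of the PhD student: "not blinded to group allocation, will conduct most in-person activities, including neurological testing, ultrasound evaluations, and intervention administration". MRI is kept apart: "A PERFORM Centre technician will administer the MRI exam". Personnel is the only section that mentions blinding.
- **What is primary.** The Methods part of the abstract lists multifidus morphology and "function (e.g., contraction measured via %thickness change from a rested to contracted state, and stiffness at rest and during contraction". The ultrasound section adds stiffness in standing.
- **How ultrasound data arise.** "The spinous process of L5 will be palpated and marked on the skin with a pen prior to imaging". The participant then lifts a loaded arm on instruction, and "Images will be taken after the loaded arm has been held for 5 s".
- **Stated safeguards.** There is a standard procedure, a reliability statement, and averaging; for stiffness, "Three repetitions will be performed on each side (both at L4-L5 and L5-S1) and the average shear wave modulus will be used for analysis".
- **MRI reading.** "The multifidus muscle CSA will be measured manually at both levels on multiple slices". The reader is not identified.
- **Analysis.** The Statistical analysis section tests every primary outcome within arms (paired t or Wilcoxon) and between arms (independent t or Mann-Whitney), at p < 0.05.
- **Order of events.** Table 1 puts Allocation in the same Baseline column as MRI, ultrasound and questionnaires.
- **Limitations.** The Discussion names treatment frequency and the BMI and age limits. It does not mention unblinded assessment.

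**The concern.** The person who acquires most of the primary measures delivers the treatment, knows the arm, and cannot help knowing whether a scan precedes or follows the 20 sessions. Locating the level, placing the probe, instructing the relaxed and contracted states and taking the image all leave room for expectation to act. This is a stated design decision, not a detail that a condensed article leaves out.

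Knowledge of the visit may shift the pre-post change. Knowledge of the arm may shift the contrast between arms. Neither is cured by more participants: a fixed artefact becomes more significant as n grows. Averaging repetitions made by the same operator does not help either, since a shift shared by all three passes straight into their mean.

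**Working it through.** **1. Which comparison carries the trial.** Inputs from the Sample size calculation section: effect size 0.9, alpha 0.05, power 80%, 12 per group raised to 15. Two-sided testing is my assumption, as the protocol gives no sidedness.

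- Paired t-test: noncentrality = d√n = 0.9 × √12 = 3.12 on 11 df, power 0.81. The smallest n reaching 80% is 12, which reproduces the stated figure. An allowance of 20% gives 12 / 0.80 = 15.
- Independent t-test: noncentrality = d√(n/2). The smallest n reaching 80% is 21 per arm. Power is 0.56 at 12 per arm and 0.66 at 15.

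The stated size therefore matches a within-arm pre-post test and not a between-arm test.

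**2. Where a shift goes.** Let δ be the true mean change in an arm and b the observer's systematic shift, both in SD of the change score.

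- Within arm A the paired test estimates δ_A + b_A, so the shift appears in full.
- Between arms the test estimates (δ_A − δ_B) + (b_A − b_B), so a common shift cancels and only a difference in shift remains.

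The comparison for which the trial was sized is thus the one with no protection against a common shift.

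**3. Illustration.** The documents give no value for b. I set δ = 0, assume a range for b, and take the probability of p < 0.05 from the noncentral t distribution. The noncentrality is b√n for the paired test and (b_A − b_B)√(n/2) for the between-arm test. For example, b = 0.5 at n = 15 gives 0.5 × √15 = 1.94 paired and 0.5 × √7.5 = 1.37 between arms.

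| Assumed shift, or difference in shift (SD of change) | Paired, n=12 | Paired, n=15 | Between arms, 12 per arm | Between arms, 15 per arm |
|---|---|---|---|---|
| 0 | 5.0% | 5.0% | 5.0% | 5.0% |
| 0.1 | 6.2% | 6.5% | 5.6% | 5.8% |
| 0.2 | 9.7% | 11.2% | 7.6% | 8.3% |
| 0.3 | 15.8% | 19.2% | 10.8% | 12.5% |
| 0.5 | 35.3% | 43.8% | 21.6% | 26.2% |

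Each entry is for one outcome and one test. At every non-zero shift the rate is higher at 15 than at 12, which shows that extra participants do not help.

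**The case against.** Several stronger readings are tempting, and the protocol does not support them.

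- **That images are measured unmasked.** A reader might infer this from the silence. The Personnel statement covers in-person work, which is acquisition. The article does not say who measures thickness, modulus, CSA or fat fraction, and the full protocol may name a masked reader. The operator dependence that is documented lies at acquisition.
- **That the MRI outcomes are equally affected.** A technician acquires the scans. The text supports the lesser point that manual CSA reading leaves room for judgement and that its masking is not described. The reliability coefficients quoted for CSA do not rule out systematic bias, but they do not show it either.
- **That Table 1 shows allocation before the baseline scan.** The Timeline section describes two pre-intervention visits. The Baseline column merges them, together with consent and the neurological screen, and shows no order. The trial treatment uses the combined setting for everyone, so it needs no allocation.
- **That the arm contrast is certainly biased.** Both arms receive active stimulation on the same device, and the protocol gives a rationale for each without predicting a winner. No direction of between-arm bias is evident, and its size may be smaller than that of the pre-post bias.
- **That the bias has a known size.** The shifts are assumed. The lower end of the 0.2 to 0.5 range gives rates near 10% for the paired test, and only the upper end gives 35% to 44%.

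It is also fair to say that masked reading does not touch acquisition, which is where the explicit problem lies. That stands, and the fix has to admit it. What remains after all this is the statement in Personnel itself, applied to primary outcomes, with no safeguard against systematic error and no mention among the limitations.

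**Conclusion.** The point holds for ultrasound. By explicit design, an unblinded treating therapist acquires the thickness-change and stiffness outcomes, and the stated safeguards do not remove systematic observer bias. The within-arm pre-post tests may be affected most.

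The size is illustrative only. With no true effect and an assumed shift of 0.2 to 0.5 SD of change, the paired test is falsely significant about 10% to 35% of the time at n=12 and 11% to 44% at n=15. A difference in shift between arms of that size gives about 8% to 22% at 12 per arm and 8% to 26% at 15. These figures assume two-sided t-tests at 0.05 and approximately normal changes.

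Masking at MRI reading and the timing of the envelope are points to confirm, not demonstrated faults. The change is worth making because it is cheap and needs no alteration to treatment, visits or sample size.

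**What to change.** 1. Store every ultrasound and elastography image. Have existing staff replace participant, arm and visit labels with random codes. The Personnel section already lists "a research assistant working for this" study's lead; that assistant's described work is recruitment and screening, so the coding task and image access would have to be assigned.
2. Make the off-line measurements after all post-intervention scans are in, in random order with baseline and 11-week images mixed. Release the codes only once the measurements are locked.
3. Apply the same masking to the manual MRI CSA reading, unless the full protocol already does.
4. State that the allocation envelope is opened only after baseline imaging and questionnaires are complete.
5. Declare in the limitations that ultrasound acquisition remains unblinded.

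**Cost.** File coding and a delay before measurement. With 30 participants × 2 visits × 2 sides × 2 levels × 3 repetitions × 5 conditions (thickness at rest and contracted; stiffness at rest, contracted and standing) there are up to 3,600 ultrasound measurements, so coding should be done in batches. The fix also assumes that stiffness can be measured from stored images, which the team should confirm. Bias from probe placement, instruction of the arm lift and choice of image stays; only an ultrasound operator masked to arm and visit could reduce it further.
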